### Data analysis

#### Preliminary data evaluation

Missing or aberrant data will be verified. Data will be audited for quality and completeness. Evaluation of distributions detects outliers and ensures that assumptions of planned analyses are met. Baseline differences between groups will be examined (e.g., IQ, demographics, psychiatric and medical comorbidity, medications). Statistical tests will not be used to select covariates in the primary intent-to-treat analysis [90–92]. Instead, the potential influences of baseline differences will be evaluated as moderators. If remedial training is given to a therapist whose adherence to the treatment protocol is not satisfactory, this will be included as a dummy-coded covariate in all analyses.

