#### Intervention fidelity

Treatment session video-recordings that occur at session 2 and at weeks 4, 8, 12 and 16 are coded using the MSRS [78] to establish the dose of memory support delivered. CT + Memory Support therapists are blind to which sessions are coded. CT-as-usual therapists are blind to the memory support portion of the research.

To reduce expectations impacting the delivery of each arm and to ensure purity of delivery [88], each treatment provider will be allocated to deliver only one of the two treatments. The rationale is that therapists report that once they have mastered memory support it is difficult to deliver CT-as-usual.

Clinicians use a treatment manual and receive weekly supervision to standardize treatment administration. Treatment sessions are video- and audio-taped and a random selection are rated using the *Cognitive Therapy Rating Scale* [89] which is a measure of general intervention skills and CBT-specific skills. The goal of this intervention is to maintain consistency and ensure adherence to the protocols [89].

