#### Missing data

Longitudinal analyses will use all available data and produce valid inferences if attrition depends on treatment group or on previous outcomes for the same participant [95]. If dropout is associated with other variables, they will be added as predictors to reduce bias due to data missing not at random.

#### Hypothesis 1

*CT + Memory Support will be superior to CT-as-usual for improving course of illness and reducing functional impairment at post-treatment, 6FU and 12FU on primary outcomes* listed in Additional file 1. Treatment groups will be compared on categorical outcomes (e.g., remission, relapse) using logistic regression to evaluate the odds of remission at post-treatment, and the odds of relapse at 6FU and 12FU. For the continuous variables (e.g., IDS-SR), we will test for differences in the mean trajectories across time between CT + Memory Support and CT-as-usual using Hierarchical Linear Modeling (HLM) [96–98]. The 1st level will represent within-person variation, and will include time indicators (or dummy variables) as predictors (post-treatment, 6FU and 12FU, with baseline as reference). The 2nd level represents between-person variation in the intercept and coefficients of the time indicators, and will include a dummy variable for arm (CT + Memory Support vs. CT-as-usual) as the predictor variable. Interactions between arm and the time indicators will be retained only if found to be significant at the 5% level using likelihood-ratio tests. Significant interaction terms between arm and time indicator suggest that there are different trajectories across time and between arms, and will be graphed to interpret the interaction.

#### Hypothesis 2

*Relative to CT-as-usual, the relationship between CT + Memory Support and better treatment outcome will be mediated by patient memory for treatment*. Outcome will be measured by IDS-SR at post-treatment, 6FU and 12FU. Patient memory will be measured by the Patient Treatment Recall Task and the Generalization Task at weeks 4, 8, 12 and 16 of treatment. A mediation model will be specified using Structural Equation Modeling [99]. Indirect effects from CT + Memory Support to better treatment outcome via patient memory will be assessed.

#### Hypothesis 3

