### Additional planned analyses

*Is CT + Memory Support associated with longer time-to-relapse relative to CT-as-usual?* Survival analyses [100] will be conducted. The Kaplan-Meier product limit method will be used to generate survival curves for the two treatment conditions [101]. Cox regression will be applied to test for group differences.
*Are demographics, psychiatric and medical comorbidity, medications and symptom severity moderators?* This will be tested by adding the product of arm and the moderator variable to regression models or HLMs [102, 103]. A significant coefficient for the interaction term would indicate a moderating effect, and will be followed up with graphs to determine the nature of the effect modification [102].
*Does memory for treatment improve simply because memory deficits resolve with successful treatment?* Linear regressions will evaluate whether change in pre-post IDS and pre-post declarative and working memory each independently predict week 4 to post-treatment differences in Patient Recall Task performance. If significant, we will conduct a hierarchical linear regression to evaluate whether pre-post change in IDS scores predicts pre-post change in Patient Treatment Recall Task performance beyond pre-post improvement in memory.
*Memory Support Rating Scale* data will be used to delineate the most effective types and combinations of memory support. Factor analysis will be used to test the structure of the *Memory Support Rating Scale* based on Lee et al. [78]. Associations between patient recall, depression outcomes, and memory support variables will be assessed.
*Number of sessions received* (range 20–26 sessions) will be added as a covariate to control for differences in this across participants.

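### A dummy for remedial therapist training, which arises after randomisation and is nested in arm, goes into every analysis and can move the primary arm effect away from the intention-to-treat effect

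*Protocol article*

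**What the plan says.** The rule is in Data analysis, Preliminary data evaluation: "If remedial training is given to a therapist whose adherence to the treatment protocol is not satisfactory", then "this will be included as a dummy-coded covariate in all analyses". Shortly before it, the same paragraph names the primary analysis as intention-to-treat and limits how covariates may enter it: "Statistical tests will not be used to select covariates in the primary intent-to-treat analysis". Under Intervention fidelity, "each treatment provider will be allocated to deliver only one of the two treatments".

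Hypothesis 1 gives the models that the rule would act on. For continuous outcomes it is an HLM with time indicators at level 1; level 2 "will include a dummy variable for arm (CT + Memory Support vs. CT-as-usual) as the predictor variable", for the intercept and for the time coefficients. Arm-by-time interactions are kept only if significant at 5%. Categorical outcomes are compared "using logistic regression to evaluate the odds of remission at post-treatment, and the odds of relapse at 6FU and 12FU".

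Two other sentences add covariates. The last item under Additional planned analyses says that number of sessions received "will be added as a covariate to control for differences in this across participants". Missing data says: "If dropout is associated with other variables, they will be added as predictors to reduce bias due to data missing not at random".

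**The concern.** An ITT comparison estimates the effect of being allocated to an arm, with treatment delivered as well or as badly as it was. Remedial training is a marker of how delivery went. It is triggered by a therapist's conduct in the trial, and because therapists are nested in arm, a patient can acquire the flag only by being allocated to that therapist's arm. This holds even if the therapist was retrained before that patient was randomised.

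If flagged therapists sit mainly in one arm and their patients do worse, the dummy absorbs that loss. The arm coefficient then leans towards a comparison among patients of therapists who needed no remediation. That may be a useful quantity, but it is not the ITT effect, and here it would be reported as the primary result of a trial that the Discussion presents as confirmatory. With flags mainly in CT + Memory Support, the benefit is overstated relative to ITT; with flags mainly in CT-as-usual, it is understated.

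**Working it through.** **Inputs.** From the article: 178 patients randomised 1:1, so 178 / 2 = 89 per arm; one treatment per therapist; the dummy in every analysis. The article states no figure for the remediation rate or for its effect on outcome, so there is nothing of the plan's own to reproduce on this point. The following are therefore assumptions, in outcome SD units with negative values better:
- d = -0.50, the arm effect among patients of unflagged therapists
- g, the outcome penalty for patients of flagged therapists
- qT and qC, the shares of CT + Memory Support and CT-as-usual patients with flagged therapists

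**Formula for a linear model at one time point.**
- ITT effect = d + g x (qT - qC)
- Effect adjusted for the dummy = d
- Shift (ITT minus adjusted) = g x (qT - qC)

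**Range of results.** The adjusted effect is -0.50 in every row.

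| qT | qC | g | ITT effect |
|---|---|---|---|
| 1/3 | 0 | 0.2 | -0.50 + 0.067 = -0.43 |
| 1/3 | 0 | 0.4 | -0.50 + 0.133 = -0.37 |
| 1/2 | 0 | 0.4 | -0.50 + 0.200 = -0.30 |
| 1/3 | 1/6 | 0.4 | -0.50 + 0.067 = -0.43 |
| 1/3 | 1/3 | 0.4 | -0.50 + 0 = -0.50 |
| 0 | 1/3 | 0.4 | -0.50 - 0.133 = -0.63 |

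A simulation with 89 per arm agreed with each row to within 0.005.

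**Precision.** Unadjusted, the standard error is sqrt(1/89 + 1/89) = 0.15. With flags in one arm only, the adjusted contrast rests on the unflagged patients of that arm. It is sqrt(1/89 + 1/59.3) = 0.17 for a share of one third, and sqrt(1/89 + 1/44.5) = 0.18 for one half.

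**Logistic model.** Assume remission of 40% in CT-as-usual, 60% under unflagged CT + Memory Support therapists and 45% under flagged ones, with qT = 1/3 and qC = 0.
- ITT remission in CT + Memory Support = (2/3)(0.60) + (1/3)(0.45) = 0.55
- ITT odds ratio = (0.55/0.45) / (0.40/0.60) = 1.83
- Adjusted odds ratio = (0.60/0.40) / (0.40/0.60) = 2.25

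**HLM with four occasions.** This used simulated mixed models with qT = 1/3, qC = 0, g = 0.4 and d = -0.50 at each post-baseline occasion.

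| Model | Arm term | Without dummy | With dummy |
|---|---|---|---|
| Interactions kept, dummy in intercept only | arm x post-treatment | -0.37 | -0.37 |
| Interactions kept, dummy also on time coefficients | arm x post-treatment | -0.37 | -0.50 |
| Interactions dropped | arm main effect | -0.27 | -0.38 |

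In the first row, a dummy that is constant over time shifts baseline and follow-up alike, so change from baseline is untouched. The last row averages over four occasions, of which baseline carries no effect: 3/4 x -0.367 = -0.275 and 3/4 x -0.50 = -0.375.

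**The case against.** The strongest reply is that the rule is conditional and may never apply. Supervision and session rating cover clinicians in general, so remediation could fall on both arms; with equal shares the linear-model shift is zero. The primary HLM may also be immune, since the article calls the dummy a covariate and mentions no interaction with time. All of this stands, and it is why the rule can bias the result rather than must. It does not rescue the rule: the logistic models have no such protection, the interactions may be dropped under the plan's own criterion, and nothing makes flags balance when therapists are nested in arm.

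Four stronger readings are tempting, and the article does not support them:
- **Sessions received biases the primary effect.** It does arise after randomisation, but it is listed among additional analyses and is not placed in the Hypothesis 1 models. If arm does not affect sessions, adjustment causes no bias.
- **Correlates of dropout are post-randomisation variables.** The article says only that they are other variables. Baseline correlates would be acceptable.
- **The dropout rule contradicts the bar on test-based covariate selection, and its aim is wrong.** The bar stands among sentences on baseline differences; the dropout rule has another purpose and mentions no test, so there is tension at most. The rule claims to reduce bias, not remove it. The wording is loose, but adding an omitted observed predictor of dropout can do that.
- **The dummy is a per-protocol exclusion.** Flagged patients stay in the model and still inform the contrast if both arms contain them.

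**Conclusion.** The point holds for the remedial-training dummy. It is a stated rule, it reaches the primary ITT analysis, and it adjusts for something that follows allocation. The size is g x (qT - qC): between 0.07 and 0.20 SD across the unequal scenarios above, and zero with equal shares. The direction depends on which arm has more remediation. In the illustrative remission example the odds ratio moves from 1.83 to 2.25. Every magnitude rests on assumed penalties, shares, remission rates and a -0.50 SD effect; the article gives none of these, so the figures show what the rule could do and do not predict what it will do. Sessions received and the dropout predictors need clarification only; they are not shown errors in the primary analysis.

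**What to change.** 1. In Preliminary data evaluation, remove the remedial-training dummy from the primary arm-comparison models. Report by arm how many therapists were remediated and how many patients they treated. If the adjusted model is wanted, present it as a sensitivity analysis labelled as not ITT.
2. In Additional planned analyses, state that number of sessions received stays out of the Hypothesis 1 models.
3. In Missing data, restrict the predictors added to the primary models for dropout to variables measured at baseline.

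The cost is a wording change. The sample size and data collection are unaffected.

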#### Multiple testing

We will use alpha = .05 for each primary hypothesis. For multiple testing conducted within each main hypothesis, we will adopt a stepwise multiple comparison procedure that is considered more powerful than the widely used Bonferroni correction [93, 94].

#### Missing data

Longitudinal analyses will use all available data and produce valid inferences if attrition depends on treatment group or on previous outcomes for the same participant [95]. If dropout is associated with other variables, they will be added as predictors to reduce bias due to data missing not at random.

#### Hypothesis 1

*CT + Memory Support will be superior to CT-as-usual for improving course of illness and reducing functional impairment at post-treatment, 6FU and 12FU on primary outcomes* listed in Additional file 1. Treatment groups will be compared on categorical outcomes (e.g., remission, relapse) using logistic regression to evaluate the odds of remission at post-treatment, and the odds of relapse at 6FU and 12FU. For the continuous variables (e.g., IDS-SR), we will test for differences in the mean trajectories across time between CT + Memory Support and CT-as-usual using Hierarchical Linear Modeling (HLM) [96–98]. The 1st level will represent within-person variation, and will include time indicators (or dummy variables) as predictors (post-treatment, 6FU and 12FU, with baseline as reference). The 2nd level represents between-person variation in the intercept and coefficients of the time indicators, and will include a dummy variable for arm (CT + Memory Support vs. CT-as-usual) as the predictor variable. Interactions between arm and the time indicators will be retained only if found to be significant at the 5% level using likelihood-ratio tests. Significant interaction terms between arm and time indicator suggest that there are different trajectories across time and between arms, and will be graphed to interpret the interaction.

#### Hypothesis 2

*Relative to CT-as-usual, the relationship between CT + Memory Support and better treatment outcome will be mediated by patient memory for treatment*. Outcome will be measured by IDS-SR at post-treatment, 6FU and 12FU. Patient memory will be measured by the Patient Treatment Recall Task and the Generalization Task at weeks 4, 8, 12 and 16 of treatment. A mediation model will be specified using Structural Equation Modeling [99]. Indirect effects from CT + Memory Support to better treatment outcome via patient memory will be assessed.

#### Hypothesis 3

The relationship between treatment condition and outcome will be moderated by poorer response subgroups; namely, older age, lower IQ, more chronic depression, poorer baseline declarative memory performance and fewer years of education. IQ will be estimated with the NART. Chronicity will be defined as current episode greater than or equal to 2 years [46]. Declarative memory will be quantified as described in Additional file 1. To assess whether Memory Support is more beneficial for any of the patient subgroups, moderation will be tested as an interaction between potential moderator and treatment arm; in the HLMs, the interaction between any of these variables, time, and treatment group will be tested.

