## Method/design

### Study design and setting

This is a prospective randomized controlled study. Adults (*n* = 178) who meet criteria for MDD will be randomly assigned, in a 1:1 parallel group design, to CT + Memory Support or CT-as-usual (see Fig. 1 for a flow chart of the study design). Randomization is stratified by age (≤49, 50 + years) and depression chronicity (< 2 years, ≥ 2 years) [46]. Participants receive a battery of outcome measures pre-treatment and post-treatment (i.e., within 2 weeks after the final treatment session) and at 6 and 12 months’ follow-up. Additional assessments of patient and therapist memory for treatment take place in weeks 4, 8, 12 and 16 of treatment for the mediation analysis.

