**Fig. 2 Fig2:**
[figure not shown]
Standard Protocol Items: SPIRIT Figure: Schedule of enrollment, interventions, and assessments

For participants who discontinue, the assessment team will endeavor to collect all assessment data, prioritizing the primary outcomes.

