#### Symptomatic

The *IDS-SR* [59], a widely used self-report measure of depression severity, as well as two subscales (ideation and behavior) from the lifetime and current version of the Columbia-Suicide Severity Rating Scale (C-SSRS) [60–62], will be administered. The *Quick Inventory for Depression Symptomatology* (QIDS) is administered every treatment session [38] for clinical purposes (monitoring of suicide and depression symptoms).

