### Treatments

Both treatments are comprised of 20–26 × 50-min sessions conducted over 16 weeks.

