#### Power analysis

Based on the pilot study [34], using Glimmpse [104, 105] for repeated measures design, we took into account the four repeated measurements (pre-treatment, post-treatment, 6FU, 12FU). At an alpha level of 0.05 with 80% power, the sample size is estimated to be 80 for the IDS-SR. We also used G*Power and the Demidenko [106] method to calculate estimated sample size for binary mood outcomes (i.e., remission, relapse). The sample sizes are estimated to be 103 (remission) and 118 (relapse). Finally, Fritz and MacKinnon [107] provide recommendations for mediation sample size, and estimates from pilot data indicate that the recommended sample size is 148. Adding an additional 20% for possible attrition, we propose a sample of 178.

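### For patients lost during treatment and not reassessed, the missing-at-random assumption rests on arm and baseline score alone; the session-by-session QIDS could strengthen it, but only as an auxiliary variable and not as an added predictor

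*Protocol article*

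**What the plan says.** All references are to the protocol article.

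- **Missing data:** the longitudinal analyses use all available data and "produce valid inferences if attrition depends on treatment group or on previous outcomes for the same participant". The next sentence adds a fallback: other variables found to be associated with dropout go into the model as predictors, to reduce bias from data missing not at random.
- **Hypothesis 1:** the first level of the HLM has "time indicators (or dummy variables) as predictors (post-treatment, 6FU and 12FU, with baseline as reference". The Power analysis agrees: "we took into account the four repeated measurements (pre-treatment, post-treatment, 6FU, 12FU".
- **Study design and setting:** "Participants receive a battery of outcome measures pre-treatment and post-treatment (i.e., within 2 weeks after the final treatment session"). The extra assessments in weeks 4, 8, 12 and 16 concern memory for treatment and serve the mediation analysis.
- **Treatments:** 20 to 26 "sessions conducted over 16 weeks".
- **Symptomatic measures:** the QIDS "is administered every treatment session [38] for clinical purposes (monitoring of suicide and depression symptoms"). No analysis described in the Data analysis or Additional planned analyses sections uses it.
- **Text after Fig. 2:** "For participants who discontinue, the assessment team will endeavor to collect all assessment data, prioritizing the primary outcomes".

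**The concern.** A likelihood-based longitudinal model protects against dropout only so far as the outcomes it contains explain that dropout. Between baseline and the post-treatment visit this model contains none. A patient may well stop because treatment is not working, or because of early recovery. Neither is visible in a baseline score, and the entry rule of IDS-SR 26 or above narrows that score's range further.

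The trial does record mood through those 16 weeks, on the QIDS, but the plan gives it no analytic role. If session mood were found to predict dropout, the one route that the text offers is to add it as a predictor. That would condition the arm comparison on something measured after randomisation and changed by treatment.

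What is at stake is the IDS-SR contrast in a trial that its Discussion presents as confirmatory. Each provider delivers only one arm (Intervention fidelity), so retention patterns that differ by arm are plausible, though the article does not report any.

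**Working it through.** **1. The plan's own figure.** The only stated number that involves dropout is the sample size: 148 × 1.20 = 177.6, rounded up to 178. It reproduces. Twenty per cent of 178 is 35.6, so about 36 patients. The article does not say how many of these would be lost during treatment.

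**2. What the model conditions on.**

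| When the patient is lost | Outcomes available to the model |
|---|---|
| During treatment, never reassessed | Baseline |
| During treatment, seen again at 6FU or 12FU | Baseline and the later score |
| After the post-treatment visit | Baseline and post-treatment |

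Only the first row is at issue.

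**3. Size of the bias.** The article gives no SD, effect, correlations or timing of attrition. All values here are assumptions:

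- true post-treatment difference -5 IDS-SR points, SD 13;
- 60% of the effect present at mid-treatment;
- correlations: baseline to post-treatment 0.4, session mood to post-treatment 0.6 to 0.75, baseline to session mood 0.5;
- 20% of each arm lost before post-treatment, with no later data.

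The dropout model is logit P(lost) = c + s × (session mood ÷ SD), with c set in each arm to give 20%. A value of s = 1 means non-improvers leave, s = -1 means improvers leave, and s = 0 means random loss. Large-sample simulation, true value -5:

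| Who leaves | Arm and baseline only | Session mood as auxiliary |
|---|---|---|
| Same rule in both arms | about -5.0 | about -5.0 |
| CT-as-usual: non-improvers; other arm: random | -4.1 to -3.7 | about -5.0 |
| CT-as-usual: non-improvers; other arm: improvers | -3.2 to -2.5 | about -5.0 |
| CT + Memory Support: non-improvers; other arm: random | -5.9 to -6.3 | about -5.0 |
| CT + Memory Support: non-improvers; other arm: improvers | -6.8 to -7.6 | about -5.0 |

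The extremes are (5 - 2.5) ÷ 5 = 50% towards the null and (7.6 - 5) ÷ 5 = 52% away from it.

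A second set of assumptions (SD 12; baseline-session, session-post and baseline-post correlations of 0.5/0.7/0.35 or 0.4/0.8/0.3; in part a steeper dependence) was run only with non-improvers leaving CT + Memory Support. It gave -6.1 to -7.2 with random loss in the other arm and -7.3 to -9.4 with opposite dependence. With the same rule in both arms it gave -4.9 to -5.0. Loss driven by arm or baseline gave -5.0, and so did 6FU when loss after the post-treatment visit followed the post-treatment score.

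**4. The fallback: session mood as a predictor.** For normal data the arm coefficient becomes

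-5 + β × (0.6 × 5), where β = (r_sp - r_bs × r_bp) ÷ (1 - r_bs²),

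with b = baseline, s = session mood and p = post-treatment.

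- r_sp = 0.6: β = (0.6 - 0.5 × 0.4) ÷ 0.75 = 0.533, so the coefficient is -5 + 1.6 = -3.4.
- r_sp = 0.75: β = (0.75 - 0.2) ÷ 0.75 = 0.733, so the coefficient is -5 + 2.2 = -2.8.

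The dropout rule does not appear in the formula. The loss of effect arises even when dropout is the same in both arms. The second set of assumptions gave -2.6 to -2.9.

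**The case against.** The strongest reply is that the quoted sentence is correct. It is a conditional statement: inference is valid if attrition depends on arm or on previous outcomes. It makes no promise for dropout that follows unmodelled mood. A reader might infer that the protection is empty. The documents do not support that: loss driven by arm or baseline is covered, and so is loss after the post-treatment visit that follows the post-treatment score. This part of the reply stands.

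Three further replies stand in part.

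- **Discontinuers are pursued.** The text after Fig. 2 commits the team to try to assess them, with the primary outcomes first, so stopping treatment is not the same as leaving the model. The effort cannot guarantee success, however, and the plan still allows 20% for attrition.
- **The plan has a fallback.** It would be wrong to say that it offers no correction. But the correction it offers, applied to session mood, distorts the arm effect.
- **The QIDS sentence gives a reason for collecting it.** A reader might take "for clinical purposes (monitoring of suicide and depression symptoms") as a bar on any other use. It does not say that. The point is only that no stated analysis uses it.

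On size, the simulation is unfavourable to the plan: it puts the whole 20% before post-treatment with nothing observed later. The auxiliary recovers -5.0 because dropout was simulated to depend on that variable. Both limits are accepted.

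It can also be said that auxiliary variables belong in a statistical analysis plan. Their absence alone would be no finding. But the rule on added predictors is fixed in this article, and it is worded so that it admits post-randomisation variables.

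**Conclusion.** The point holds as an inexpensive improvement and not as an error in the validity sentence. For patients lost during treatment and not reassessed, the IDS-SR model relies on arm and baseline alone. The stated fallback would make matters worse if session mood were put through it.

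Bias in the contrast needs dropout that depends on in-treatment mood differently in the two arms. Under the assumed values an effect of -5 was then estimated anywhere from about -2.5 to -7.6; without such a difference the bias was negligible. A reader might infer that the plan understates the benefit. The documents do not support any direction, because the sign depends on which arm loses its non-improvers. Fewer unassessed losses during treatment than the assumed 20% would mean a smaller bias.

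The shrinkage to about -2.8 to -3.4 from the fallback does not need differential dropout. It does depend on the assumed 60% of the effect being present at mid-treatment and on the assumed correlations.

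**What to change.** 1. In **Missing data**, state that session-level QIDS serves as an auxiliary variable for missing IDS-SR, either through multiple imputation done separately by arm or as an additional outcome in a joint longitudinal model.
2. In the same section, restrict the added predictors to baseline variables, so that anything measured after randomisation enters only as an auxiliary.
3. In **Symptomatic** measures, add this analytic use of the QIDS beside the clinical one.

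The QIDS is already administered at every session in both arms, so no new data collection is needed. The cost is a few sentences, modest programming, and cleaning and locking the session QIDS as research data.

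### The Hypothesis 1 mixed model names arm as its only between-person predictor, so it omits the randomisation strata and uses baseline inefficiently; this costs precision, not validity

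*Protocol article*

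**What the plan says.** Under Study design and setting the article states: "Randomization is stratified by age (≤49, 50 + years) and depression chronicity", with chronicity cut at 2 years and allocation "in a 1:1 parallel group design".

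Under Data analysis, Hypothesis 1, the HLM for continuous outcomes is written out. Level 1 has time indicators ("post-treatment, 6FU and 12FU, with baseline as reference"). Level 2 models between-person variation in the intercept and in the time coefficients, and "will include a dummy variable for arm (CT + Memory Support vs. CT-as-usual) as the predictor variable". For binary outcomes the text is shorter: "Treatment groups will be compared on categorical outcomes (e.g., remission, relapse) using logistic regression". It gives no covariate list for those models.

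Preliminary data evaluation rules out choosing covariates by significance test in the primary intent-to-treat analysis. It names no prespecified prognostic covariates in their place: "Instead, the potential influences of baseline differences will be evaluated as moderators". Age and chronicity return only under Hypothesis 3, as moderators.

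Three other covariates are mentioned: a dummy for remedial therapist training, if it occurs; predictors of dropout, if any are found; and number of sessions, under Additional planned analyses. None is stated to be a stratification factor.

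**The concern.** The Background says that older age and chronic depression predict poorer response to treatment for depression, including cognitive therapy, and it cites the same source as the stratification. If the two factors are important enough to balance at randomisation, their variance should not be left in the error term of the primary contrast. Under stratified allocation, a model without the strata also reports a standard error larger than the design warrants.

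Arm on the intercept lets each arm have its own baseline mean, although randomisation makes the two expected means equal. The model spends information estimating a difference known to be zero in expectation, and the arm-by-time coefficient becomes a change-score contrast.

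Sending baseline differences to moderator analyses does not repair this. A moderator test asks whether the effect varies between patients; it leaves the Hypothesis 1 estimate unadjusted for chance imbalance. What is at stake is the precision of a trial that the Discussion presents as a definitive test.

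**Working it through.** **The plan's own figure.** Under Power analysis, 148 × 1.20 = 177.6, which rounds to the stated 178. The component sizes (80 for IDS-SR, 103 for remission, 118 for relapse, 148 for mediation) cannot be reproduced, because the article gives no effect size, SD, event rate or correlation. Everything below therefore rests on assumed ranges, with two-sided alpha 0.05 and a normal approximation.

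**Baseline.** Take one follow-up visit with follow-up SD 1, baseline SD k, and baseline-to-follow-up correlation r. Per-patient variance behind the arm contrast:

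- planned (unconstrained baseline, change score): 1 + k² − 2rk
- baseline as covariate, or baseline means constrained equal: 1 − r²

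Power, for a change-score comparison that has 80%, becomes Φ(2.802 × √(planned/adjusted) − 1.960).

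| k | r | planned | adjusted | ratio | 80% power becomes |
|---|---|---|---|---|---|
| 1 | 0.3 | 1.40 | 0.91 | 0.65 | 93.5% |
| 1 | 0.5 | 1.00 | 0.75 | 0.75 | 89.9% |
| 1 | 0.7 | 0.60 | 0.51 | 0.85 | 86.0% |
| 0.7 | 0.3 | 1.07 | 0.91 | 0.85 | 85.9% |
| 0.7 | 0.5 | 0.79 | 0.75 | 0.95 | 82.0% |
| 0.7 | 0.7 | 0.51 | 0.51 | 1.00 | 80.0% |

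With k = 1 the ratio simplifies to (1 + r)/2. A generalised least squares calculation for the four planned visits (compound symmetry, 74 per arm) gave the same 0.65, 0.75 and 0.85 for the post-treatment contrast. The k = 0.7 rows are there because entry requires an IDS-SR score of at least 26, which cuts off the lower part of the baseline distribution. The value 0.7 is itself an assumption.

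**Strata.** Stable level differences between strata already cancel in a change contrast, so R² here means the share of the variance in change that age and chronicity explain.

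- Power after adjustment: Φ(2.802/√(1 − R²) − 1.960). For R² = 2%, 5% and 10%, 80% becomes 80.8%, 82.0% and 84.0%.
- Actual level of a nominal 5% test that ignores the strata: 2 × [1 − Φ(1.960/√(1 − R²))] = 4.8%, 4.4% and 3.9%. This assumes that the allocation keeps the arms closely balanced within strata.
- Under the same close balance, the unadjusted test has true power Φ(0.842/√(1 − R²)), about 80 to 81% rather than exactly 80%. The gain of 1 to 4 points is therefore at the generous end.

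**Logistic models.** This arithmetic does not carry over. Adding a prognostic covariate generally does not shrink the standard error of a log odds ratio; it moves the target from a marginal to a conditional odds ratio. The benefit is power and handling of chance imbalance.

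**The case against.** The strongest reply is that the plan is valid as written and that Hypothesis 1 has room to spare. By the article's own figures IDS-SR needs 80, remission 103 and relapse 118, while the trial is sized at 148 for mediation before attrition is added. Rejecting test-based covariate selection is good practice and does not rule out prespecified adjustment. All of this stands, and it limits the urgency. It does not make the HLM efficient, and the remedy needs no new data.

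A second reply is that a condensed article may leave covariates to the full protocol or analysis plan. That stands for the logistic models, where the text neither lists nor excludes covariates. It does not stand for the HLM, whose level-2 predictor is stated.

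Four stronger readings are tempting and not supported:

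- A reader might infer that the primary models contain nothing but an arm dummy. The HLM also has time indicators, and conditional covariates are mentioned elsewhere. The accurate statement is that arm is the only between-person predictor named in that model.
- A reader might infer that the remission and relapse analyses are planned without baseline severity. The article is silent on this.
- A reader might infer that the omission biases the comparison or inflates type I error. Under randomisation it does neither for the arm-by-time contrast; the test is, if anything, mildly conservative.
- A reader might translate the equal-SD ratios into 15 to 35% fewer patients. That shows only the favourable case; with a narrower baseline SD the saving is 15%, 5% or nothing.

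**Conclusion.** The point holds for the HLM as a matter of efficiency. The model as stated omits both stratification factors and leaves baseline means unconstrained, and no moderator analysis adjusts the primary estimate.

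The size cannot be fixed from the article. Over the assumed range the baseline loss runs from substantial (variance ratio 0.65) to none (1.00), depending on the correlation and on how far the entry cutoff narrows the baseline SD. The strata loss is small and exists only if age and chronicity predict change, which the Background makes plausible but does not quantify. With variances treated as known, the adjusted contrast is never less precise than the planned one. For the logistic models the point is a recommendation to specify, not an error found.

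**What to change.** **HLM.** Prespecify age stratum and chronicity stratum as fixed covariates with time interactions. Then either constrain baseline means to be equal across arms, or use baseline as a covariate with post-treatment, 6FU and 12FU as the outcomes.

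If baseline means are constrained, the arm-by-time terms carry the whole treatment effect. The rule that "Interactions between arm and the time indicators will be retained only if found to be significant at the 5% level" could not then apply, and the terms must stay in the model.

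**Logistic models.** Prespecify the two strata and baseline IDS-SR, and state whether the reported effect is a conditional odds ratio or a standardised (marginal) one.

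**Moderator analyses.** Keep them for effect modification only, not as the response to baseline imbalance.

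**Cost.** A short revision of the analysis section and a decision on the odds ratio to report. Age, chronicity and IDS-SR are already collected at entry, so no extra patients or procedures are needed.
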